On the second visit day for the baseline evaluation and the first treatment, all patients will also complete the PSQI, ISI, BDI, STAI, K-AVLT, and the DS, with HRV measured at baseline (prior to first treatment), after the last treatment, and at the 1-week follow-up. EEG recordings will be used as objective measures to validate self-reported insomnia symptoms. ERPs will be measured at baseline and after the last treatment using an odd-ball task. Spontaneous EEGs will also be measured at baseline after the last treatment for spectral analysis. All subjects will complete the WHOQOL-BREF at baseline and at 1-week follow-up. They will also complete the Temperament Character Inventory (TCI) at baseline. All patients will also complete a sleep log every day from baseline to the 1-week follow-up [27]. The Credibility of Treatment Rating Scale (CTRS) will be administered to assess the maintenance of blind conditions after the second treatment [28].

Registered patients shall be randomly divided into the experimental and sham control groups, with an equal number of patients assigned to each group. Patients will then complete either the experimental or sham acupuncture treatment 3 times, with 2- to 3-day intervals, within 1 week.

Figure 1 is an overview of this trial, and Figure 2 is an approximate visit schedule.

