### Sample size

Sample size was calculated based on a ratio of 1:1 between the experimental and control groups. This sample size is based on a study that investigated the effect of acupuncture treatment on insomnia using ISI as a primary outcome [30]. In that study, the mean change in ISI between the experimental and control groups was 3.8 and the standard deviation was estimated as the median between the experimental (SD =4.0) and control groups (SD =3.2). Based on a two-tailed alpha error of 5% and with a statistical power of 80%, the calculated sample size is based on the equation:

Therefore, all 38 participants will be randomly assigned with 19 subjects in each group, assuming a 20% dropout rate.

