### Statistical method

The primary outcome variable for efficacy analysis is ISI, and secondary outcomes are the PSQI, BDI, STAI, WHOQOL-BREF, sleep logs, K-AVLT, DS, EEG, and HRV. Demographics, sleep logs, ISI, PSQI, K-AVLT, Digit Span, STAI, TCI, EEG, and HRV will be analyzed using independent sample *t*-tests at baseline to determine equality of the two groups. A chi-square test will be used to assess sex differences. An efficacy analysis will be done using both per-protocol and intention-to-treat analyses.

Independent *t*-tests between the two groups and a repeated-measures analysis of variance (ANOVA) will be used to determine and compare the effect of acupuncture. The factors are treatment (3 levels: pre-, post-acupuncture and 1-week follow-up) and groups (2 levels: treatment and sham) and their interaction. The significance level was set at *P <*0.05 and *post-hoc* analyses were performed where appropriate.

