## Abbreviations

AEs: adverse events
ANCOVA: analysis of covariance
BDI: Beck Depression Inventory
CRF: case report form
CTRS: Credibility of Treatment Rating Scale
DS: Digit Span Test
DSM-IV: The Diagnostic and Statistical Manual of Mental Disorders, Fifth Edition
EEG: electroencephalogram
ERPs: Event Related Potentials
HF: high frequency
HRV: heart rate variability
IDA: intradermal acupuncture
IRB: Institutional Review Board
ISDC-2: International Classification of Sleep Disorders, Second Edition
ISI: Insomnia Severity Index
K-AVLT: Korean-Auditory Verbal Learning Test
LF: low frequency
PSQI: Pittsburgh Sleep Quality Index
STAI: State-Trait Anxiety Inventory
STRICTA: Standards for Reporting Interventions in Clinical Trials of Acupuncture
TCI: Temperament Character Inventory
WHOQOL-BREF: World Health Organization Quality of Life Abbreviated Version.

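### The efficacy analysis makes no covariate adjustment for baseline ISI, which is already collected; the planned tests are valid but mostly less efficient than ANCOVA

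*Protocol article*

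**What the plan says.** The protocol's Statistical method section names two kinds of efficacy test: independent t-tests between the groups and a repeated-measures ANOVA. Its description of the ANOVA is complete: "The factors are treatment (3 levels: pre-, post-acupuncture and 1-week follow-up) and groups (2 levels: treatment and sham) and their interaction". The pre-treatment ISI is thus a level of the response. No covariate appears, and the section does not say whether the t-tests use raw or change scores, or which ANOVA term is the efficacy test.

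For baseline comparability, the same section lists demographics and the main measures, ISI among them, which "will be analyzed using independent sample *t*-tests at baseline to determine equality of the two groups".

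Baseline ISI is available for every patient before treatment starts. The Setting section says: "On the second visit day for the baseline evaluation and the first treatment, all patients will also complete the PSQI, ISI, BDI, STAI". The Primary outcome section defines the outcome as change in ISI across baseline, post-treatment and the 1-week follow-up. The list of abbreviations contains "ANCOVA: analysis of covariance", but the article's text never uses the term.

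**The concern.** In a randomized trial with a pre-treatment measurement of the primary outcome, the usual efficient analysis uses that measurement as a covariate. The protocol instead treats it as a response or, depending on how the t-tests are done, subtracts it or leaves it out.

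Three things follow.
- If the t-tests use post-treatment scores, chance baseline imbalance stays in the estimate. If they use change scores, baseline is subtracted with a slope of 1, which over-corrects unless the baseline-to-post correlation is close to 1.
- The group main effect of the ANOVA averages in a visit at which randomization makes the true difference zero.
- The baseline t-tests ask whether a difference could be due to chance when, after proper randomization, any difference is due to chance.

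In a trial sized for about 15 completers per arm, the power and precision lost in this way are worth recovering.

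**Working it through.** **Inputs from the Sample size section.** "the mean change in ISI between the experimental and control groups was 3.8"; "the standard deviation was estimated as the median between the experimental (SD =4.0) and control groups (SD =3.2", taken here as the midpoint (4.0 + 3.2)/2 = 3.6; two-sided alpha 5%, power 80%, allocation 1:1, 20% dropout.

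**Reproducing the plan's figure.** n per arm = 2(1.960 + 0.842)² × 3.6²/3.8² = 14.1, rounded up to 15. Then 15/0.80 = 18.75, rounded up to 19 per arm, 38 in total. This matches. Power at 15 per arm is 82.4% by the normal approximation and 79.7% by the t distribution.

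**Assumptions not in the documents.** The baseline-to-post correlation r is not given; 0.3, 0.5 and 0.7 are used, with equal variances and equal correlations across the three visits. The text does not settle whether 3.6 is the SD of the ISI score or of its change, so both readings are shown. The effect is 3.8 points at both post-baseline visits.

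**Formulas, with σ the SD of the score and 15 per arm.** Under the score reading σ = 3.6. Under the change reading σ = 3.6/√(2(1−r)) = 3.04, 3.60, 4.65.
- Post-score t-test: SD σ, 28 df.
- Change-score t-test: SD σ√(2(1−r)), 28 df. Score reading: 4.26, 3.60, 2.79. Change reading: 3.6 throughout.
- ANCOVA of the post score: residual SD σ√(1−r²), 27 df, with the variance inflated on average by 27/26 for chance imbalance in the covariate. Score reading: 3.43, 3.12, 2.57. Change reading: 2.90, 3.12, 3.32.
- Group-by-time interaction: F on 2 and 56 df, noncentrality (15 × 3.8²/3)/(σ²(1−r)) = 72.2/(σ²(1−r)). Score reading: 7.96, 11.14, 18.57. Change reading: σ²(1−r) = 3.6²/2 = 6.48, so 11.14 throughout.
- Group main effect: expected difference (0 + 3.8 + 3.8)/3 = 2.53, two thirds of the effect; SD of the three-visit mean σ√((1+2r)/3), 28 df.

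**Power (%) at r = 0.3 / 0.5 / 0.7**

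| Test | 3.6 is SD of score | 3.6 is SD of change |
|---|---|---|
| ANCOVA, post score | 82 / 88 / 97 | 92 / 88 / 84 |
| Post-score t-test | 80 / 80 / 80 | 91 / 80 / 58 |
| Change-score t-test | 65 / 80 / 95 | 80 / 80 / 80 |
| Group-by-time interaction | 69 / 84 / 97 | 84 / 84 / 84 |
| Group main effect | 72 / 63 / 55 | 85 / 63 / 36 |

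Simulation agrees to within about 1.5 points.

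**ANCOVA against the interaction.** Score reading: gains of about 12 to 13, 5 and 0 points. Change reading: about 8 to 9, 5 and 0 to 1. These hold for a sustained effect. If the effect halves by follow-up, the simulated interaction power at r = 0.5 falls to about 71%, while ANCOVA at the post-treatment visit is unaffected.

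**Near zero correlation.** At r = 0 under the score reading, ANCOVA has 78.1% against 79.7% for the post-score t-test, a loss of 1.6 points.

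**Baseline tests.** With 19 per arm, a two-sided 5% t-test reaches 80% power only for a true difference of about 0.93 SD, so a non-significant result cannot show equality. If the baseline SD is also 3.6 (an assumption), the standard error of chance imbalance at 15 per arm is 3.6√(2/15) = 1.31 points, about a third of the 3.8-point target.

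**The case against.** The strongest defence is that the ANOVA includes the interaction. With outcomes at pre, post and follow-up, group-by-time tests differential change, which is how the primary outcome is defined, and it uses baseline by differencing. At a correlation of 0.7 it matches ANCOVA for a sustained effect. This stands, and it limits the size of the point.

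A reader might infer that the t-tests ignore baseline altogether. The documents do not support that: both the outcome definition and the sample size speak of change, so change-score tests are at least as natural a reading. A reader might also take the group main effect, with its 55 to 72% or 36 to 85% power, as the efficacy test. No section says so, and the two-thirds dilution matters only if it were used that way.

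Nor does the protocol attach any decision to the baseline tests, so it would be inference to say that they will drive the choice of covariates. The unused ANCOVA abbreviation is an editorial loose end; it may reflect a fuller document and does not show that ANCOVA was planned and dropped.

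It may also be said that covariates are left to an analysis plan. That carries less weight here, because the article states its tests and factors positively, and the comment concerns that stated choice.

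**Conclusion.** The point holds as a recommendation on efficiency. Over correlations of 0.3 to 0.7 and under both readings of the SD, ANCOVA has more power than either t-test and than the group main effect. Against the interaction, its advantage for a sustained effect runs from nil to about 12 or 13 points and is about 5 points at a correlation of 0.5. The size rests on a correlation that the documents do not give, on the unsettled meaning of the 3.6, and on equal correlations across visits. Near zero correlation ANCOVA loses 1 to 2 points against a post-only t-test, so the gain is not strictly free.

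It would go too far to call the planned analysis invalid or the trial undersized by its own calculation: the tests hold their error rate under their usual assumptions, and 38 follows from the stated inputs. The baseline tests for equality are uninformative, but they do not themselves bias the efficacy comparison.

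**What to change.** In the Statistical method section, make the primary analysis an ANCOVA of post-treatment ISI on group with baseline ISI as covariate. The alternative is a mixed model of the two post-baseline visits with group, visit, their interaction and baseline ISI as covariate, so that baseline is no longer a response level. State the estimated between-group difference with its confidence interval.

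Use the same form for each secondary outcome that has a baseline value, at the visits where it is measured. Replace the baseline t-tests and the chi-square test for sex with a descriptive table by group, without P values. Then either use the ANCOVA entry in the abbreviations or remove it.

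The cost is wording and one degree of freedom for the covariate: no new data, visits or patients. The sample size can stay at 38, since the correlation is unknown and should not be relied on to reduce it.

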### Monitoring

A qualified clinical trial expert will monitor this study. This trial in particular will be monitored by [name], OMD, PhD, a research professor at the College of Korean Medicine, Kyung Hee University. [name] is a professional clinical research associate, having completed a formal training program organized by the Korea National Enterprise for Clinical Trials. Monitoring will commence after the first participant completes the entire period of this study.

### Ethical considerations

The Institutional Review Board (IRB), prior to subject recruitment, has already approved the entire design and procedure of the clinical trial, CRF, and all measures that will be used in the study (reference number KHNMC-OH-IRB 2011-015, IRB at Kyung Hee University Gangdong Medical Center, approved on the 13 September 2012). All subjects must provide written informed consent prior to study participation.

The trial will be performed in accordance with the principles of good clinical practice of the Korean Food and Drugs Administration and/or the Declaration of Helsinki 2008.

## Discussion

Standards for Reporting Interventions in Clinical Trials of Acupuncture (STRICTA) were revised in 2010, yet few studies have rigorously observed these recommendations. Consequently, the results of many previous studies likely do not meet standards of objectivity and methodology. In our proposed study, all details such as acupoints, verification tools, and use of acupuncture needles and procedures will be reported objectively following STRICTA standards.

Previous trials of acupuncture treatment have focused only on subjectively reported symptoms of insomnia. Consequently, they are not able to observe the mechanisms of acupuncture’s effect on insomnia. In the present trial, HRV will be used to assess changes in the autonomic nervous system and EEG will be used to assess changes in brain activity in real time. These measures will objectively examine physiological changes due to acupuncture in real time.

Depression, anxiety, and decline in cognitive functions are the main consequences of chronic insomnia as reported by many previous studies, and such symptoms ultimately degrade quality of life. The effect of acupuncture on insomnia will be verified at multi-dimensional levels in this trial, assessing psychological and emotional states, cognitive functions, and quality of life, allowing us to observe how the relief of insomnia symptoms due to acupuncture treatment improves patients’ quality of life.

In the trial, we will test the intradermal acupuncture method particularly for enhancing the effectiveness of acupuncture for insomnia. The acupuncture is stimulated every night by subjects applying it continuously on their own, even at home.

The design of the control group in studies verifying the effect of acupuncture treatment is always an issue. For this blind-controlled study, STRICTA suggests active acupuncture control, penetrating needle control, or non-penetrating sham needling control. The present proposed trial will use 'sham’ acupuncture points as active acupuncture control. However, it is possible that sham acupuncture may lead to improvement. Such a methodological limitation should be improved upon in future studies. A double-blind trial is not possible because of the particular treatment method of the controls. This limitation will be addressed with an evaluation by an experimenter who is not involved in the treatment. Furthermore, there are limitations associated with the lack of polysomnographic data due to constraints of time, expense, and space in the hospital, as the present trial is still a pilot study. The actigraphy and polysomnography are objective tools for assessing insomnia and are also highly recommended, but many other studies have used them as secondary outcomes while still others did not use actigraphy and/or polysomnography as outcomes at all [31–33, 10, 11]. However, polysomnography will be assessed in our planned future expanded trials.

## Trial status

This clinical trial is currently recruiting participants.

## Abbreviations

AEs: adverse events
ANCOVA: analysis of covariance
BDI: Beck Depression Inventory
CRF: case report form
CTRS: Credibility of Treatment Rating Scale
DS: Digit Span Test
DSM-IV: The Diagnostic and Statistical Manual of Mental Disorders, Fifth Edition
EEG: electroencephalogram
ERPs: Event Related Potentials
HF: high frequency
HRV: heart rate variability
IDA: intradermal acupuncture
IRB: Institutional Review Board
ISDC-2: International Classification of Sleep Disorders, Second Edition
ISI: Insomnia Severity Index
K-AVLT: Korean-Auditory Verbal Learning Test
LF: low frequency
PSQI: Pittsburgh Sleep Quality Index
STAI: State-Trait Anxiety Inventory
STRICTA: Standards for Reporting Interventions in Clinical Trials of Acupuncture
TCI: Temperament Character Inventory
WHOQOL-BREF: World Health Organization Quality of Life Abbreviated Version.
